## 7.2 Management of young people and viral load tests during the Pilot Phase

Current PCR tests for HIV-1 RNA can occasionally yield spurious results suggestive of low level viremia. Any HIV-1 RNA measurement that is detected at  $\geq 50$  c/ml at weeks 1, 2 or 3 will be repeated on the **SAME SAMPLE** to ensure that the result is valid and reproducible. All participants in the pilot phase will have an additional visit at week 8.

### SCT arm:

Any participant with a reproducible viral load of  $\geq 50$  c/ml (2 tests on the SAME sample) after the first weekend off treatment will not have a break over the 2nd weekend. On the Monday visit on week 2 after having taken medications at the weekend, the viral load will be repeated (confirmatory test).

- If this result is  $\geq 50$  c/ml then the participant should not undertake any further interruptions.
- If the confirmed test is  $< 50$  c/ml, then the child may undergo a second interruption over the third weekend. If the young person has a 2nd reproducible viral load  $\geq 50$  c/ml (2 tests on the SAME sample) after the third weekend, the young person should not undertake any further interruptions.

For further details please see appendix 15

Once the 15th participant randomised to the SCT arm has been recruited to the pilot phase screening and randomisation will be put on hold in both arms. The IDMC will meet at the end of the pilot phase when the 15th participant randomised to the SCT arm has completed 3 weeks (or 4 weeks if they require a confirmatory viral load for a sample at 3 weeks), to review the information collected and make recommendations to the Trial Steering Committee about the continuation of the trial (see section 11.5).

Young people in both arms enrolled during the pilot phase will continue to be followed as per randomised arm in the main phase of the trial.

### Continuous ART arm:

Participants will be seen during weeks 1, 2 and 3 for blood store and viral load measurement (not necessarily on a Monday). If a viral load result of  $\geq 50$  c/ml is reproducible, clinic staff should discuss adherence to continuous ART with the young person.

## 7.3 Specific Requirements for the Main Trial

Participants enrolled in the main phase of the trial will be able to choose the days off (Friday-Saturday or Saturday-Sunday)\*. Whichever is chosen must be continued throughout the entire time on SCT within the study.

\*Consecutive days off alternative to Saturday-Sunday or Friday-Saturday can be chosen to better suit a young person's normal routine.

The two days off ART treatment indicated by the participant at screening should be confirmed on the Trial Entry form. It should be made very clear that the chosen 2 days off should remain the same throughout the length of the trial.

Participants in the main phase of the trial should be asked to come to the randomisation visits as soon as possible following the screening visits (once eligibility has been confirmed and within a maximum of 4 weeks), having fasted from the previous evening.

A full clinic visit should be scheduled for 4 weeks after the randomisation visit i.e. a week 4 visit.

## **7.4 Management of young people and viral load tests during the Main Trial for the SCT arm**

Participants with a HIV-1 RNA measurement  $\geq 50$  c/ml will have a confirmatory viral load measurement on a **SEPARATE SAMPLE** within 1 week. No further interruptions to antiretroviral therapy should be undertaken until the repeat test result is obtained.

Participants with a confirmed viral rebound of  $\geq 50$  c/ml should re-commence continuous ART and should not undergo further interruptions to their therapy.

Participants with an isolated increase of HIV-1 RNA  $\geq 50$  c/ml and subsequent measurement  $< 50$  c/ml can remain on SCT. There can only be a maximum of 3 such occurrences over any 12 month period. After the third increase within 12 months, continuous ART should be resumed with no further interruptions.

Note: Viral load results with a higher cut-off than 50 c/ml e.g.  $< 80$  c/ml (due to technical issues, diluted samples or low volume) should not be considered a blip, but participants should still be instructed to return to clinic for a re-test to confirm their viral load is  $< 50$  c/ml.

For further details please see Appendix 15.

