(e) Pregnancy Test: either a blood or urine sample. This test will be performed for all females of childbearing potential at screening and weeks 24 and 48 (then every 24 weeks) and at other time-points if required. The initial pregnancy test must be done within 72 hours of enrolment and its results must be received before randomisation.

(f) Weeks 1,2,3 phlebotomy visits should be before recommencing ART on the Monday; sufficient blood should be sent to the virology laboratory for a repeat measurement of the same sample.

(g) 16ml total blood draw in EDTA for plasma and cell storage: 6.0ml in EDTA if plasma store only (see Manual of Operations for instructions for plasma and cell handling and storage).

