Data on viral dynamics in the first few days following treatment cessation are scarce. Jacobsen *et al* in a 4-arm study of PTI  $\pm$  HIV immunisation reported viral rebound to >50 c/ml following treatment interruption at a median (interquartile range) of 15 (8 to 31) days for those with prior PTI and of 21 (13 to 30) days for those without prior PTI [24]. Harrigan *et al*, whilst assuming a constant rate of viral increase that starts as soon as the patient stops therapy, suggest that many patients stopping therapy (previously suppressed) will have increases in plasma viral HIV RNA of about 0.2 log/day and will only reach detectable levels (>50 c/ml) within 1 to 2 weeks of stopping therapy [34].

A substudy of PENTA 11 evaluated the pharmacokinetics, viral load rebound and resistance profiles in 35 children stopping non-nucleoside reverse transcriptase inhibitor (NNRTI) based ART [35]. 21 children followed a staggered stop (SS) strategy whereby the NNRTI (NVP or EFV) was stopped at randomisation and the remaining 2 NRTI drugs stopped 7-14 days later, and 14 children followed a replacement strategy (RS) whereby the NNRTI was replaced with a PI and all drugs stopped 7-

14 days later. Results of HIV viral load testing in 8 children following SS and 7 following RS strategies show that the majority of children still had undetectable HIV RNA 5-8 days after stopping all drugs (minimum 12 days after stopping the NNRTI) (Table 1). No NNRTI resistance mutations were detected in any of the children in the substudy.

**Table 1: Viral loads (c/ml) 5-8 days after 1st interruption, stopping ALL drugs in 15 children in the PENTA 11 PK substudy**

| Strategy | NNRTI | Days after stopping ALL drugs |     |                   |     |
|----------|-------|-------------------------------|-----|-------------------|-----|
|          |       | 5                             | 6   | 7                 | 8   |
| SS       | EFV   | <50                           |     |                   | <50 |
|          | NVP   | <50, <50                      | 159 | <50, 89, 7000     |     |
| RS       | EFV   |                               |     | <50               | <50 |
|          | NVP   |                               |     | <50, <50, 52, 707 | 70  |

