## **7.6 The continuous ART arm**

Young people randomised to continuous ART should continue on their current antiretroviral therapy and should follow standard local practice at subsequent visits, including checking ART doses at every visit and adjusting for body surface area or weight as necessary.

A full clinic visit should be scheduled for 4 weeks after the randomisation visit i.e. a week 4 visit.

If the HIV-1 RNA increases to  $\geq 50$  c/ml at any time, the participant should be brought in for a confirmatory measurement on a separate sample within 1 week and should be managed as per standard clinical care.

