## 11.3 Sample size

This phase II/III trial will enrol a minimum of 160 young people, at least 80 per arm.

Assuming 90% of young people in the continuous ART arm and in the SCT arm maintain HIV-1 RNA  $< 50$  c/ml to week 48, 155 young people will provide at least 80% power to exclude a difference of 12% between the two arms (i.e. to exclude suppression rates of less than 78% in the SCT arm) (one-sided  $\alpha = 0.05$ ) [37]. A minimum of **160 (80 per arm) young people will be enrolled** to allow for loss to follow-up (in previous PENTA trials loss to follow-up has been less than 3%).

The power calculations are based on the assumption that 90% of patients in the continuous ART arm will remain virally suppressed to week 48. Any decrease in this percentage is likely to under

power the study and could lead to an equivocal result, as could other changes to the assumptions. The table below gives an indication of the power to exclude a difference of 12% between the two arms for different sample sizes and levels of suppression in the continuous ART arm:

| Total sample size | Power by level of suppression in control arm |                |                |                |                |                |
|-------------------|----------------------------------------------|----------------|----------------|----------------|----------------|----------------|
|                   | 90% suppressed                               | 89% suppressed | 88% suppressed | 87% suppressed | 86% suppressed | 85% suppressed |
| 160               | 80                                           | 77             | 74             | 72             | 69             | 67             |
| 170               | 82                                           | 79             | 76             | 74             | 72             | 69             |
| 180               | 84                                           | 81             | 79             | 76             | 74             | 72             |
| 190               | 86                                           | 83             | 81             | 78             | 75             | 74             |
| 200               | 87                                           | 85             | 82             | 80             | 78             | 76             |
| 210               | 89                                           | 86             | 84             | 82             | 79             | 77             |

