| 220               | 90                                           | 88             | 85             | 83             | 81             | 79             |

A sample size of 220 participants would increase the power of the study by at least 10% for varying levels of suppression. The TSC and IDMC therefore agreed that the study should remain open to randomisation until the end of the defined recruitment period even should the total number of participants enrolled exceed 160, as this would enhance the power of the study as indicated in the table above. The total recruitment target should be at least 160 but not exceed 220 participants.

The trial is not formally powered to detect differences between continuous ART and SCT, but to exclude substantial virological disadvantages (i.e. HIV-1 RNA suppression rates (<50 c/ml) of less than 78%) to the SCT arm by following a 5 days on, 2 day off strategy i.e. a non-inferiority trial.

A non-inferiority margin of 12% was chosen to represent a clinically acceptable difference in the rate of virological suppression <50 c/ml between the two arms, and to allow the trial to be adequately powered and feasible to conduct based on estimates of available young people followed in PENTA centres.

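### In the main trial a raised viral load in the SCT arm is confirmed while breaks are suspended, so break-related viraemia that re-suppresses can go uncounted in that arm only; the size is unknown

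*Combined protocol and SAP*

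**What the plan says.** The primary outcome (sections 4.2, 11.2 and 11.6) is HIV-1 RNA of at least 50 c/ml at week 4, 12, 24, 36 or 48, confirmed on a separate sample within a week.

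For an SCT participant with a first raised value in the main trial, section 7.4 states: "No further interruptions to antiretroviral therapy should be undertaken until the repeat test result is obtained". Section 1.5 and Appendix 15 carry the same rule. If the repeat is below 50 c/ml, the rise is an isolated increase and the participant may stay on SCT. A third such rise within 12 months ends SCT, but is not defined as a primary event. After a recent immunisation (section 7.7) the repeat waits until two weeks after vaccination, with the young person back on continuous treatment.

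In the continuous arm (section 7.6) the participant is to be "brought in for a confirmatory measurement on a separate sample within 1 week" and managed by standard care. No change from the assigned strategy is required.

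Sampling time is fixed only in the pilot SCT arm. Flowsheet 1.9 says: "Weeks 1,2,3 phlebotomy visits should be before recommencing ART on the Monday". For the main trial, section 7.3 says only: "A full clinic visit should be scheduled for 4 weeks after the randomisation visit i.e. a week 4 visit". Flowsheet 1.11 gives week numbers, with no weekday and no interval since the break.

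For pilot participants, sections 4.2 and 11.6 count a value of at least 50 c/ml at weeks 1 to 3, reproduced on the same sample, as a primary event at week 4.

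**The concern.** Confirmation is meant to remove assay noise. In the continuous arm it asks whether viraemia persists under the assigned strategy. In the SCT arm, from week 4, it asks whether viraemia persists once breaks have been stopped. A rise caused by the break that falls again on ART fails that test and is not counted. The free sampling day adds to this: a first sample taken some days after the restart may miss such a rise altogether.

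Section 2.6 gives two routes to the main risk of SCT: viral load not staying below detection during the two days off, and participants extending the break. The main-trial endpoint is least sensitive to the first route. The pilot rule treats the same rise differently, because there later re-suppression does not cancel the event.

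Any under-count confined to SCT shrinks the observed difference. In a non-inferiority trial that is the anti-conservative direction.

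**Working it through.** **1. The plan's own figure.** Section 11.3: "Assuming 90% of young people in the continuous ART arm and in the SCT arm maintain HIV-1 RNA" below 50 c/ml to week 48, and "155 young people will provide at least 80% power to exclude a difference of 12% between the two arms", at one-sided alpha 0.05. With unpooled variance:

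n per arm = (0.90×0.10 + 0.90×0.10) × (1.645 + 0.842)² / 0.12² = 77.28, so 154.6 in total, which rounds up to 155.

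Dividing by 0.97 for 3% loss gives 160. All 42 cells of the power table reproduce within 2.0 points (160 at 90%: 81.2 against the printed 80). Sample size is not at issue.

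**2. How large a break-related rise could be.** Section 2.4 cites "increases in plasma viral HIV RNA of about 0.2 log/day". Two days give 10^0.4 = 2.5-fold, so the starting level that reaches 50 c/ml is 50/2.51 = 19.9 c/ml. Only someone already at about 20 c/ml or more would cross the threshold. Such rises would be low-level and could plausibly fall again on ART, but they may also be uncommon.

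**3. Effect on the error rate.** Take true failure at the margin, 10% against 22%. Let d be the percentage points of SCT failure left unconfirmed, with no equivalent loss in the continuous arm. **d is an assumption; the documents give no value.** Then

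P(non-inferiority) = Φ[(0.12 − observed difference)/SE − 1.645], with SE = √[(0.10×0.90 + p(1−p))/n] and p = 0.22 − d.

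Example, d = 2 points, n = 80: SE = √(0.25/80) = 0.0559; (0.12 − 0.10)/0.0559 − 1.645 = −1.287; Φ = 0.099.

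| d (points) | Observed SCT failure | 80 per arm | 110 per arm |
|---|---|---|---|
| 0 | 22% | 5.0% | 5.0% |
| 2 | 20% | 9.9% | 11.0% |
| 3 | 19% | 13.5% | 15.7% |
| 6 | 16% | 30.4% | 37.6% |

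The upper end supposes that half of the 12-point excess is transient. The error is larger at 110 per arm because more participants estimate the shifted difference more precisely.

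**4. What the pilot can rule out.** Section 11.5 treats 4 or fewer rises among 15 SCT participants as reassuring. The binomial chance of that result is 78% if the true off-ART rate is 22%, and 52% if it is 30%. Passing the pilot is limited evidence that break-related rises are rare.

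**The case against.** A reader might infer that break-related viraemia is systematically logged as a blip, that the comparison is biased, and that the real error rate is 10-30%. The documents do not support this.

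- The 2-6 points have no source. Section 2.4 gives the 0.2 log/day rate on the assumption that growth starts as soon as therapy stops, and still puts detectable levels at 1 to 2 weeks. It also gives efavirenz a plasma half-life of 36-100 hours. In its Table 1 all four efavirenz results were below 50 c/ml at 5 to 8 days after stopping all drugs. In the randomised adult five-on-two-off trial (section 2.3) there were 6 blips in the intermittent arm and 9 in the daily arm. Such rises may well be uncommon.
- Sustained rebound would still be confirmed and counted.
- Recall in the continuous arm may improve adherence and turn some of its rises into blips too, so part of the loss may be shared.
- Suspension starts only once a result is known. A quick repeat may involve no missed break. Appendix 15 counts the week from the report of the result, so with slow reporting a break can precede the repeat.
- HIV-1 RNA below 50 c/ml at weeks 24 and 48 is a secondary outcome with no confirmation step.
- The IDMC found no safety concern in the pilot.
- Section 11.6 places the full SAP in a separate document, so a planned sensitivity analysis cannot be excluded.

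It is also tempting to infer that a participant is always sampled on the weekday of randomisation. Section 7.3 speaks only of week 4, and days off are chosen individually.

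These points limit certainty and probable size. They leave the difference between arms in place. The unconfirmed secondary outcome covers two of the five primary visits and has no stated margin. The pilot rule covers weeks 1 to 3 of about 15 SCT participants out of at least 80.

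**Conclusion.** The point holds as a possibility with a known direction and an unknown size. From week 4 the SCT arm's confirmatory sample is taken while breaks are suspended, the continuous arm's is not tied to any change of strategy, and sampling time relative to the break is left open. Break-related viraemia that re-suppresses can therefore escape the primary endpoint in SCT only, which can favour non-inferiority. The error rates in the working hold only under their assumed 2-6 points and under no matching loss in the continuous arm; with no such viraemia there is no distortion. This does not show that a non-inferiority result would be wrong. It shows that the confirmed endpoint cannot settle the matter by itself, and that data already collected could.

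**What to change.** Leave clinical management and the primary endpoint unchanged.

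1. Pre-specify a supporting analysis in both arms: the difference in failure, with its 90% confidence interval, set against the margin. ("A non-inferiority margin of 12% was chosen" in section 11.3, and one-sided 5% corresponds to a 90% interval.) The event is the first HIV-1 RNA of at least 50 c/ml at week 4, 12, 24, 36 or 48, (a) unconfirmed and (b) reproduced on plasma stored at that visit. SCT stopped after three isolated rises also counts as failure. Only SCT has that stopping rule, so report how many events come from it alone.
2. Tabulate SCT viral loads by time since the scheduled break, derived from visit dates and the days off on the Trial Entry form.
3. Interpret the non-inferiority conclusion alongside both.

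The cost is one analysis, one table and re-assay of the stored samples from visits with a raised value. Flowsheets 1.11 and 1.12 store plasma at all five visits, and section 8.5 names viral load testing as a purpose.

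The drawback is noise, since unconfirmed values include assay blips. If unconfirmed suppression were 75-80% in both arms (assumed), power at 80 per arm would be about 54-60%: at 80%, 0.12/√(2×0.16/80) − 1.645 = 0.252, and Φ = 0.60. The analysis should therefore be supportive, not a gate on the primary conclusion.

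Moving SCT blood draws to just before the first dose after the break is not suggested. It would sample one arm at its worst point and reverse the asymmetry. Section 18 puts the end of recruitment at June 2013 and this protocol version at May 2015, so the week 4 to 48 visits were already over. If the 48-week comparison has been seen, label the added analysis post hoc.

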## **7.5 Considerations for the SCT arm for both Pilot Phase and Main Trial**

### **7.5.1 Forgetting to stop antiretrovirals**

If a patient in the SCT arm forgets to stop taking their medication for one or both of the days during their pre-defined break they will need to continue with taking the medication during the 5 days on and then stop at the next, pre-defined break.

### **7.5.2 Follow-up after re-starting continuous ART due to viral rebound in the SCT arm**

The participant should be seen at weeks 4 and 12 and then 12-weekly (see flowsheet section 1.12). ART should be continued without any further days off. Participants in the SCT arm who restart therapy should complete an acceptability questionnaire at the point of restarting treatment.

Any changes in the antiretroviral regimen are at the discretion of the clinician but should be discussed with the appropriate Trials Unit. Participants resuming continuous ART should follow standard local practice at subsequent visits, including checking ART doses at every visit and adjusting for height and weight as necessary and should be followed until the end of the trial. Forms should be completed at each follow up visit.

## **7.6 The continuous ART arm**

Young people randomised to continuous ART should continue on their current antiretroviral therapy and should follow standard local practice at subsequent visits, including checking ART doses at every visit and adjusting for body surface area or weight as necessary.

A full clinic visit should be scheduled for 4 weeks after the randomisation visit i.e. a week 4 visit.

If the HIV-1 RNA increases to  $\geq 50$  c/ml at any time, the participant should be brought in for a confirmatory measurement on a separate sample within 1 week and should be managed as per standard clinical care.

## 7.7 Immunisation

If a viral load increase has occurred within two weeks of the participant having received an immunisation, the confirmatory viral load test should be performed immediately after the young person is two weeks post vaccination. The young person should go back to continuous treatment following the viral load increase and should remain on ART until the result of the confirmatory second sample is known.

## 7.8 Trial products

Regimens containing 2 NRTIs/NtRTIs and EFV will be included.

### SCT Arm

At the end of each 2-day-SCT, participants must re-start the same regimen for the following 5 days.

### Both Arms

For both arms, if a change in antiretroviral therapy is indicated the appropriate Trials Unit should be contacted and this should be recorded on the appropriate CRF (including reasons and dates of any changes).

## 7.9 Dispensing

Routine supplies of ART will be used; clinical trial labels will be supplied for participants in the SCT arm. A dispensing log should be completed for each patient. Clinics must check that families have an ABC alert card if the participant is taking abacavir (ABC).

